#### Self-Efficacy

As for motivation, participants’ self-efficacy level will also be assessed at T1 and T2 by auto-captured data on the platform using a visual analog 10-point Likert scale (ie, If you decided to increase your level of physical activity, how confident would you be in your ability to succeed? 0=somewhat confident and 10=extremely confident). Visual analog scales have been shown in several studies to be a valid method that allows individuals to visually estimate their sense of self-efficacy [75,76].

#### Feasibility

The following feasibility parameters will be assessed: (1) recruitment (ie, the proportion of eligible patients who agree to participate in the study), (2) retention (ie, the proportion of participants who complete the intervention), (3) adherence (the proportion of sessions and activities completed), and (4) fidelity to the intervention (ie, the difference between the planned and delivered intervention). Due to anticipated recruitment challenges and because the refusal rate during recruitment of older adults generally varies from 20% to 50% [77], we consider it feasible to achieve a recruitment rate of 70% for the desired sample size (n=21 older adults) in the given recruitment time (ie, 1 year). Of this number, we will aim to obtain a retention rate of 75% of the participants for completion of the intervention and data collection (n=16 older adults), considering that a retention rate of about 70%-80% is observed in similar studies of web-based interventions with populations of older adults [36,78,79].

#### Qualitative Component

For the qualitative component, we will assess the acceptability (question 1) and the impacts (question 3) of the intervention. Semistructured interviews will be conducted 1 week post intervention (T2) by a Master’s student, a member of the research team who is unbiased and trained in conducting interviews. The interview guide was developed to address research questions 1 and 3. The acceptability questions were drafted on the basis of the characteristics of an intervention as outlined by Sidani and Braden [80], that is, structure and content. The impact questions were designed to assess the qualitative impact on the various outcomes of the study (ie, physical activity level, quality of life, knowledge, motivation, and self-efficacy). The interviews will last approximately 30 minutes and will be conducted by phone. Acceptability will be assessed through data collected on the intervention’s structure (ie, delivery mode, number of sessions, frequency, and duration) and content (ie, information and activities proposed) to determine whether participants found the intervention appropriate to their situation and relevant in supporting their engagement in physical activity [81]. During the interviews, we will also evaluate the impacts of the intervention, as perceived by the participants, on their physical activity level, quality of life, knowledge, motivation, and self-efficacy (eg, Have you noticed any changes since participating in the *Changeons ensemble* intervention? If so, please tell us about the changes in your physical activity level). The interview guide was pretested with the patient-partner who contributed to the development of the intervention.

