**Methods:**

A web-based nursing intervention was developed according to the Intervention Mapping framework in collaboration with a team of health care professionals (n=5) and based on the needs of older adults (n=10). The 7-week intervention (1 session per week) aims to support older adults living with coronary artery disease in resuming, maintaining, or increasing their level of physical activity after coronary bypass surgery or percutaneous coronary intervention. The intervention offers educational content on coronary heart disease and physical activity, suggestions for physical activity, reflective activities, case histories of older adults who have experienced different journeys, an electronic physical activity diary to track progress, and support from a nurse through feedback to increase knowledge, motivation, and sense of self-efficacy. The preliminary effects and impacts of the intervention will be assessed through a mixed method pilot study with a sequential explanatory design. First, a single-group pre-post test will be used to assess the intervention’s preliminary effects on physical activity (electronic journal), quality of life (36-Item Short Form Health Survey version 2), knowledge (quiz), motivation, and self-efficacy (visual analog scale) of 30 older adults living with coronary heart disease, as well as the feasibility of the intervention. Second, a descriptive qualitative design will use semistructured interviews to assess the intervention’s impacts as perceived by 8-12 older adults and its acceptability. Quantitative data on the effects of the intervention will be integrated with the collection and analysis of qualitative data to assess the impact perceived by older adults, using matrices. Nonparametric statistics and a thematic analysis will be produced. A joint display will be used to integrate mixed data.

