### Design

A pilot study with an explanatory sequential mixed design (quantitative→qualitative) [51,52] will be conducted to evaluate the intervention’s preliminary effects and impacts. The mixed sequential explanatory design implies that a quantitative method is followed by a qualitative one [51,52]. Therefore, the quantitative method for evaluating the preliminary effects of the intervention will be carried out first, followed by the qualitative method for evaluating the benefits perceived by older adults as a result of the intervention.

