#### Qualitative Component

We will contact the 30 older adults who took part in the intervention by phone to invite them to participate in the qualitative evaluation, with the goal of recruiting 8-12 participants. As suggested by several authors [61,62], we estimate that we will need 8-12 participants to reach data saturation regarding their perceptions of the intervention’s impacts and its acceptability. Since the study requires a long-term commitment from the participants, we may not be able to reach the desired number of participants for the qualitative analysis. These results will form part of the assessment of the project’s feasibility.

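### Interviews one week after each participant finishes, by open invitation, leave group results unable to inform qualitative collection and rest acceptability on 8-12 self-selected people

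*Protocol article*

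**What the plan says.** **Design.** The Design section labels the study explanatory sequential: "The mixed sequential explanatory design implies that a quantitative method is followed by a qualitative one". It adds that the quantitative evaluation comes first. The abstract (Methods) extends the link to data gathering: "Quantitative data on the effects of the intervention will be integrated with the collection and analysis of qualitative data".

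**Timing.** Under Data Collection, Qualitative Component: "Semistructured interviews will be conducted 1 week post intervention (T2"). Recruitment (Setting and Sample) and data collection (Data Collection) share one window, June 2024 to June 2025. The Results section reports 20 enrolled as of April 2025.

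**Guide.** "The interview guide was developed to address research questions 1 and 3", and "The interview guide was pretested with the patient-partner who contributed to the development of the intervention".

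**Selection.** In the Qualitative Component part of Setting and Sample, the article states: "We will contact the 30 older adults who took part in the intervention by phone to invite them to participate in the qualitative evaluation". The goal is 8-12 interviewees.

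**Acceptability.** It is part of the primary research question. Table 1 marks its quantitative column as not applicable and gives interviews as its source.

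**Integration.** Data Integration (Mixed Component) describes a joint display that sets quantitative and qualitative results side by side.

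**The concern.** There are two linked problems.

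First, in an explanatory sequential design the quantitative results help decide whom to interview and what to ask. The abstract promises a link of that kind, but the procedures provide none. The guide was built for questions 1 and 3 and pretested before any results existed, the invitation goes to everyone, and interviews are tied to each person's own finish. A reader of the final report would credit the interviews with an explanatory role that their conduct did not give them.

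Second, half of the primary question depends on who accepts the invitation. People who stopped, or who used the platform little, are well placed to say that its structure or content did not suit them. They may also be the least inclined to give an interview at a time defined by the end of the intervention. If they are absent, the acceptability conclusion that informs a larger evaluation could be too favourable, and the reader could not tell. The Limitations section discusses convenience sampling into the study, not self-selection into the interviews.

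**Working it through.** **1. The plan's own counts (Feasibility section).** Recruited: 0.70 × 30 = 21. Retained: 0.75 × 21 = 15.75, rounded up to 16. Both stated figures reproduce. Expected non-completers: 21 − 16 = 5, and 5/21 = 24%.

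**2. Can group results precede the interviews?** The intervention lasts 7 weeks and the interview follows 1 week later, so a person who starts in week s is interviewed in week s + 8. The last participant, who starts in week L, reaches T2 in week L + 7, or L + 8 if T2 coincides with the interview. An interview precedes the last T2 when s + 8 < L + 7, that is, when s is more than 1 week before L. In the L + 8 case any earlier start is enough.

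Assumption: N participants enrolled evenly over 44 weeks (roughly June 2024 to April 2025) or 52 weeks (the full window). The tightest spacing is 44/29 = 1.5 weeks, which exceeds 1 week, so every slot except the last participant's falls before the last T2:

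| N | Slots before the last T2 |
|---|---|
| 16 | 15 |
| 20 | 19 |
| 21 | 20 |
| 30 | 29 |

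The counts are the same for both enrolment lengths and both T2 timings.

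**3. Could the interviews wait?** If they were held back until the last T2, the first completer would wait 44 to 52 weeks after finishing and the median completer 22 to 26 weeks. That is incompatible with a 1-week interval.

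**4. Coverage of the acceptability sample.**

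| Base | 8 interviews | 12 interviews |
|---|---|---|
| 30 (enrolment goal) | 27% | 40% |
| 21 (recruitment target) | 38% | 57% |
| 16 (retention target) | 50% | 75% |

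A share proportional to the 5 expected non-completers would be 8 × 5/21 = 1.9 to 12 × 5/21 = 2.9 interviews. The plan contains no step that secures any.

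**5. Illustration of what is unknown.** Assume that 80% of interviewees find the intervention acceptable. The share among all 21 lies between (0.8 × 8)/21 = 30% and (0.8 × 8 + 13)/21 = 92% with 8 interviews, and between (0.8 × 12)/21 = 46% and (0.8 × 12 + 9)/21 = 89% with 12. These are worst-case and best-case bounds, not forecasts. They show how far the answer depends on who is not heard.

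**The case against.** Stronger readings are tempting, and the documents do not support them.

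- *The sequential design fails altogether.* A reader might infer that no quantitative result can reach an interview. Within one person, however, the T2 measures can precede or accompany the interview, and a semistructured guide leaves room for probing. Only group-level results are out of reach; individual results are available, but the article describes no use of them.
- *Question 4 cannot be answered.* It asks how interview findings supplement and illuminate the quantitative effects, not what caused them. The joint display can serve that purpose, so question 4 stands as written.
- *Non-completers are excluded and acceptability will be biased upward.* The invitation covers all who took part and is made by phone, which can reach people who have left the platform. A positive lean is plausible, not certain. Any consented interview involves some self-selection.

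It is also fair to say that an article may leave guide revision and interviewee selection to a fuller document, and that the figure summarising the protocol steps is not shown. This does not dispose of the point. The article states whom it invites and when it interviews, and those statements do not fit the abstract's claim about collection. The study is a single-group pilot that disclaims generalisation, which lowers the stakes without removing them, because acceptability is a primary question.

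**Conclusion.** The concern holds in limited form. At group level, the stated order and the abstract's link to qualitative collection cannot both be met alongside 1-week interviews during staggered enrolment. As described, integration takes place when results are brought together, which is closer to a convergent design. Separately, acceptability rests on 8-12 self-selected people, with no provision that low adherers or any of about 5 in 21 non-completers are among them.

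The timing result assumes even enrolment. That interviews run on a rolling basis is inferred from the dates and the 1-week interval; the article does not say so. The non-completer count takes the plan's retention target as the outcome. The direction of any bias in acceptability is a possibility and its size is unknown.

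**What to change.** 1. Replace the open invitation with simple purposive selection on completion and adherence, both already logged for feasibility. Reserve a few of the 8-12 places for non-completers or low adherers who consent. Keep to these two factors: 8-12 places cannot fill a finer grid, and T1-T2 change may be missing for people who stopped.
2. Report interviewees' completion and adherence beside those of all enrolled.
3. Where a person's T1-T2 results exist, raise them only after the open questions on perceived impact, so that they do not steer those answers.
4. With 20 enrolled by April 2025 and collection due to end in June 2025, interviews may be too far advanced for this. In that case, describe the design as convergent with integration at interpretation, correct the abstract's reference to collection, and limit the acceptability conclusion to those interviewed.

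The cost is a little scheduling work, with no added interviews. Some non-completers may decline; the number approached and refusing should then be reported.

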### Data Integration (Mixed Component)

For a mixed explanatory sequential design study, some authors propose developing a joint display (refer to Figure 3 for an example). Joint display allows for the presentation of integrated quantitative data (eg, statistical) and qualitative data (eg, verbatim) [82]. In this study, quantitative data on the effects of the intervention will be integrated into the qualitative results [51] of the older adults’ perceptions of the impacts of the intervention. The quantitative results will be integrated into the qualitative results to illustrate how the quantitative effects of the intervention can be connected to the qualitative impacts on physical activity level, quality of life, knowledge, motivation, and feelings of self-efficacy (question 4). To this end, we will follow the four steps proposed by Johnson, Grove, and Clarke [83], which are (1) listing, that is, listing data in the quantitative data (statistics) or the qualitative data (verbatims or categories) column; (2) matching, that is, matching quantitative data with qualitative data based on their similarity, patterns, or parallels; (3) checking, that is, verify whether the data are matched correctly; and (4) pillar building, that is, comparing and contrasting the findings from the last steps to build proposals based on patterns and insights in the integration themes column, to help clarify connections between the data.

**Figure 3 figure3:**
[figure not shown]
Example of joint display.

### Analysis

The sample will be described using descriptive statistics (eg, mean, SD, percentage, and frequency). Descriptive statistics will also be used to compare, between pre- and postintervention, participants’ level of physical activity, knowledge, motivation, and self-efficacy as well as feasibility data. The Wilcoxon signed rank test will be performed to compare the results from the SF-36v2 questionnaire. Statistical analyses will be performed using QualityMetric’s PRO CoRE system [84]. Semistructured interviews will be recorded and transcribed verbatim, and a thematic analysis [85] will be performed using MAXQDA Analytics Pro (VERBI Software GmbH) 2022. The data will be analyzed by the student researcher (AL) and validated by her supervisor (VD). Themes and subthemes will be identified from the verbatim transcripts and then grouped according to their complementarity, similarity, recurrence, or divergence to form salient thematic clusters. The links between these themes will be further explored to create thematic groupings, and a thematic tree will be developed in the form of a diagram [85].

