#### Quantitative Component

For the quantitative component, a single-group pre-post test design will be used to evaluate quantitatively the preliminary effects of the intervention on physical activity level, quality of life, motivation, knowledge, and self-efficacy. This quantitative component is presented according to the SPIRIT (Standard Protocol Items: Recommendations for Interventional Trials) checklist [53], presented in Multimedia Appendix 2.

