#### Quantitative Component

To assess the preliminary effects of the intervention, we will seek to enroll 30 older adults living with CHD. According to some authors, 30 participants are sufficient for a pilot study [56,57], and this sample size is found in similar studies [58,59]. Given that we are interested in a vulnerable clientele that has a low participation rate in CR programs [14] and in research projects in general [60], we anticipate some challenges in terms of both recruitment and retention of participants. As the primary aim of this study is to explore preliminary effects, acceptability, and feasibility, a larger sample size was not deemed necessary at this stage.

Older adults will be recruited by the student researcher by convenience sampling during their hospitalization for coronary bypass graft surgery or a percutaneous coronary intervention. The first author (AL) will screen each patient’s record to verify eligibility and then meet with the eligible patients to evaluate their interest in participating in the project after their hospitalization. Eligibility criteria for participation in this study will be (1) 65 years or older; (2) agreement to participate in the study within 3 months post hospitalization for a coronary bypass graft surgery or 1 month for a percutaneous coronary intervention; (3) no concurrent involvement in an intervention designed to increase their level of physical activity (eg, a CR program, consultation with physical activity expert) during their participation in the project; (4) fluency in French, spoken and written; (5) access to a computer or a tablet connected to the internet; and (6) no cognitive impairments according to the patient record (ie, decreased or impaired complex attention, executive functions, learning abilities, memory, or social skills). Recruitment will take place from June 2024 to June 2025.

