#### Quality of Life

The French Canadian version of a quality-of-life questionnaire (36-Item Short Form Health Survey version 2 [SF-36v2] [65]) will be completed by participants at T1 and T2 via LimeSurvey (Jason Cleeland). This questionnaire has 36 items to answer on 3-, 5-, and 6-point Likert scales, with a higher score indicating a better quality of life. It covers eight concepts: physical functioning, bodily pain, role limitations due to physical health problems, role limitations due to personal or emotional problems, emotional well-being, social functioning, energy, fatigue, and general health perceptions. The SF-36v2 is a revised and improved version of the SF-36 [69]. The SF-36v2 has good psychometric properties with internal consistency reliability ranging from 0.83 to 0.95, test-retest reliability ranging from 0.64 to 0.86, and median correlations of items to their scales ranging from 0.612 and 0.87 [69].

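### No outcome is given an estimate of within-person change with its uncertainty: four are only described and the SF-36v2 is only tested

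*Protocol article*

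**What the plan says.** The Design section of the protocol article states that "a single-group pre-post test design will be used to evaluate quantitatively the preliminary effects of the intervention", and lists five outcomes: physical activity level, quality of life, motivation, knowledge and self-efficacy. Data Collection schedules each of them at T1 (before) and T2 (after) and assigns them to question 2, the question on preliminary effects.

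The Analysis section then splits the methods. For physical activity, knowledge, motivation and self-efficacy it says "Descriptive statistics will also be used to compare, between pre- and postintervention" the participants' levels. For quality of life it says "The Wilcoxon signed rank test will be performed to compare the results from the SF-36v2 questionnaire". The sentence before these, on describing the sample, shows what kind of statistic is meant: "The sample will be described using descriptive statistics (eg, mean, SD, percentage, and frequency".

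On the instrument, the Quality of Life section says "It covers eight concepts" and names neither a summary score nor a leading scale. On numbers, the plan is that "we will seek to enroll 30 older adults living with CHD". The Feasibility section adds that "we consider it feasible to achieve a recruitment rate of 70% for the desired sample size (n=21 older adults", and aims for 75% of those to complete the intervention and data collection (16 people).

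**The concern.** A single-group pilot can say one useful thing about effects: how much each person changed, and how precisely that is known. The stated methods do not produce this for any outcome. Physical activity, the behaviour the intervention targets and the first outcome named in the question on preliminary effects, gets a description without an interval. The SF-36v2 gets a test, which yields a P value but not the size of the change.

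Two further risks follow from what the wording permits.

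- **Drop-out.** The section does not limit the descriptive comparison to people with both measurements. With about a quarter expected not to complete, summaries at T1 and T2 could rest on different people, and a shift in the mean could reflect who left.
- **Multiplicity.** The SF-36v2 has eight scales, and nothing marks its tests as exploratory. One scale could reach significance by chance, and the Data Integration section carries the quantitative results into the joint display.

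**Working it through.** **1. The plan's own numbers.** From Setting and Sample and from Feasibility: 30 × 0.70 = 21 recruited; 21 × 0.75 = 15.75, rounded up to 16 retained. Both figures reproduce. Non-completers: 21 − 16 = 5.

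**2. Precision of a paired change.** The half-width of a 95% t interval for a mean change, in units of the SD of the change, is t(0.975; n − 1)/√n.

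| People with both values | Half-width (SD of change) |
|---|---|
| 16 (planned completers) | 0.53 |
| 21 (all recruited, no loss) | 0.46 |
| 30 (full target, no loss) | 0.37 |

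Separate means and SDs at T1 and T2 do not give this interval. The variance of the change is SD₁² + SD₂² − 2r·SD₁·SD₂, and the within-person correlation r cannot be recovered from the two summaries.

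**3. Drop-out shift, if T1 used 21 people and T2 used 16.** Suppose no individual changes, and the 5 non-completers start d baseline SDs below the 16 completers. The T1 mean of all 21 then lies (5/21) × d below the completers' mean, and the T2 mean equals the completers' mean. The apparent change is therefore (5/21) × d. The documents give no value for d, so a range is assumed.

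| Assumed gap d | Apparent change |
|---|---|
| 0.25 SD | 0.06 SD |
| 0.5 SD | 0.12 SD |
| 1.0 SD | 0.24 SD |

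A paired change among the 16 is exactly zero in each of these cases.

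**4. Multiplicity, if all eight scales were tested.** The article states neither the number of tests nor a significance level; eight tests at a two-sided 0.05 are assumed. With independent scales, the chance of at least one false positive is 1 − 0.95⁸ = 0.337. Simulating eight equally correlated change scores with no true change (n = 16, Wilcoxon signed rank test, 3,000 runs per setting) gives:

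| Assumed correlation between scales | At least one P < 0.05 |
|---|---|
| 0 | 31% |
| 0.3 | 28% |
| 0.5 | 24% |
| 0.7 | 19% |

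Across the formula and the simulation, the range is about 19% to 34%.

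**The case against.** The strongest reply is that much of this is silence rather than error. A journal article condenses a fuller protocol, and intervals, analysis sets and multiplicity rules are commonly left to that protocol or to an analysis plan. Description without testing is a defensible choice for secondary outcomes in a pilot of 30 whose primary question is acceptability and feasibility. The Limitations section already concedes the lack of a control group and of generalisability.

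Three stronger readings are tempting, and the document does not support them.

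- A reader might infer that T1 and T2 will be summarised separately on different people. The text does not say so; a descriptive comparison can be of paired change among completers. The list of means, SDs and percentages belongs to the sentence on describing the sample.
- A reader might infer that the SF-36v2 analysis ignores the pairing or could be driven by drop-out in the same way. It could not: the Wilcoxon signed rank test works on within-person differences, so a change in who is measured cannot create its result. Completers may still be a selected group.
- A reader might infer that eight P values are planned. The article refers only to the questionnaire's results. Multiplicity also cannot apply to the four outcomes that are not tested.

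The reply reduces the weight of the point but does not remove it. The Analysis section does more than omit detail: it allocates a method to each outcome, and neither method, as named, is an estimate of change with its uncertainty.

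**Conclusion.** The point holds in a limited form and is minor. Followed as written, the Analysis section yields a description for four outcomes and a test for the fifth, and an estimate of within-person change with an interval for none. That mismatch with the question on preliminary effects rests on the text alone. At 16 completers, the imprecision left unreported is about ±0.53 SD of change.

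The other two figures are conditional. The shift of 0.12 to 0.24 SD needs both unmatched summaries (21 before, 16 after) and a baseline gap of 0.5 to 1 SD. The 19% to 34% chance of a false positive needs all eight scales tested at 0.05, with correlations between scales of 0.7 down to 0. They show what the wording leaves open, not what is known to be planned. Because effects are a secondary question in a pilot, neither risk threatens the study's main purpose.

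**What to change.** Reword the Analysis section as follows.

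- For all five outcomes, report the paired change (T2 minus T1) among participants with both values, as a mean or Hodges-Lehmann median change with a 95% confidence interval, and state the number of pairs.
- Show T1 values of completers and non-completers side by side. The paired analysis removes the shift in composition, but completers may still be selected.
- Keep the Wilcoxon signed rank test for the SF-36v2; the Hodges-Lehmann estimate is its natural companion.
- Label the SF-36v2 scale results exploratory and carry that label into the joint display. Intervals alone do not remove multiplicity. Naming one leading scale in advance is an option, not a requirement.

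The cost is a few sentences and a small amount of extra analysis. No new data, visits or participants are needed.

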### Aim and Research Questions

The purpose of this study is to evaluate a web-based nursing intervention to support older adults living with CHD in engaging in physical activity. This study aims to answer the following questions:

Primary research questionWhat is the acceptability (content, structure, and usefulness) and feasibility (recruitment, retention, adherence, and fidelity) of a web-based nursing intervention to support older adults living with CHD in engaging in physical activity?Secondary research questionsWhat are the preliminary effects of the web-based nursing intervention on the physical activity level and quality of life of older adults living with CHD?What are the qualitative impacts of the web-based nursing intervention as perceived by older adults on their physical activity level, quality of life, motivation, knowledge, and self-efficacy?How do the qualitative findings on perceived impacts from older adults post intervention complement and illustrate the preliminary quantitative effects of a web-based nursing intervention developed for this population?

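### Retention, part of the primary question, has a 75% target but only a descriptive summary; at 21 to 30 participants it needs an interval, and adherence needs a per-participant summary

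*Protocol article*

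**What the plan says.** In the protocol article, the primary question under Aim and Research Questions asks about acceptability together with "feasibility (recruitment, retention, adherence, and fidelity) of a web-based nursing intervention".

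The Feasibility section gives numerical targets for two of the four parameters:

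- **Recruitment** is defined as "the proportion of eligible patients who agree to participate in the study". The target, however, is 70% of the desired sample of 30, that is 21 people within one year.
- **Retention**: "we will aim to obtain a retention rate of 75% of the participants", given as 16 people. The reason offered is that "a retention rate of about 70%-80% is observed in similar studies".
- **Adherence** is defined as "adherence (the proportion of sessions and activities completed". There is no target, and the unit and denominator are not stated.
- **Fidelity** is the gap between what was planned and what was delivered, with no target.

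The sample size rests on the statement that "30 participants are sufficient for a pilot study" and on the size of comparable studies, not on precision. The Analysis section describes the sample with "descriptive statistics (eg, mean, SD, percentage, and frequency" and applies descriptive statistics also to "knowledge, motivation, and self-efficacy as well as feasibility data". The one test it names, the Wilcoxon signed rank test, is for the SF-36v2, which belongs to a secondary question.

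**The concern.** The plan sets a numerical aim for a primary feasibility measure and then states a method that attaches no uncertainty to it. With about 21 participants, one person more or less moves retention by nearly 5 points (1/21 = 4.8%). The range used to justify the target is only 10 points wide. A reader who sees 76% beside a 75% target, with nothing else, will take retention as shown to be adequate. A reader who sees 71% (15/21) will take it as shown to be inadequate. The data could support neither conclusion.

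This matters because the Results section says the findings will feed into refining the intervention, and the Discussion says they could lead to a larger evaluation.

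Adherence raises a related reporting problem. A single percentage of sessions and activities could be formed in several ways. Some of them hide whether many people did part of the programme or a few did none of it.

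**Working it through.** **Inputs from the protocol article.** Desired sample 30; recruitment target 70%; retention target 75%; counts 21 and 16; retention in comparable studies 70% to 80%; refusal among older adults 20% to 50% (Feasibility). Seven weekly sessions (Abstract, Methods). No confidence level is stated, so two-sided 95% is assumed here.

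**1. The plan's own counts.** 0.70 × 30 = 21. 0.75 × 21 = 15.75, rounded up to 16. Both reproduce.

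**2. Precision of retention at the target.** The exact (Clopper-Pearson) limits for x of n are the 2.5% quantile of Beta(x, n−x+1) and the 97.5% quantile of Beta(x+1, n−x).

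| Result | Percentage | Exact 95% CI | Wilson 95% CI |
|---|---|---|---|
| 16/21 | 76.2% | 52.8% to 91.8% | 54.9% to 89.4% |
| 23/30 (0.75 × 30 = 22.5, rounded up) | 76.7% | 57.7% to 90.1% | 59.1% to 88.2% |

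The exact interval at 16/21 is 91.8 − 52.8 = 39.0 points wide; at 23/30 it is 90.1 − 57.7 = 32.4 points wide. Both are more than three times the 10-point range from which the target was drawn.

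**3. Chance of reaching the retention target.** P(X ≥ 16) for X ~ Binomial(21, p), and P(X ≥ 23) for X ~ Binomial(30, p):

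| True retention p | At least 16 of 21 | At least 23 of 30 |
|---|---|---|
| 50% | 0.013 | 0.003 |
| 60% | 0.096 | 0.044 |
| 70% | 0.363 | 0.281 |
| 75% | 0.567 | 0.514 |
| 80% | 0.769 | 0.761 |
| 85% | 0.917 | 0.930 |
| 90% | 0.986 | 0.992 |

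Between 70% and 80%, where the protocol expects to be, the result can easily fall on either side. At 60% or below the target of 16 of 21 is missed at least 1 − 0.096 = 90.4% of the time. At 85% or above it is met at least 91.7% of the time.

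**4. Recruitment: two different quantities.** The defined rate is agreeing divided by eligible. The target of 21 is a count against the planned 30. The documents do not say how many eligible patients will be approached. The cited refusal range implies 50% to 80% agreement. At 80% agreement, 21 participants would come from about 26 eligible patients (21/0.80 = 26.25); at 50%, from 42 (21/0.50). The same count of 21 therefore fits very different agreement rates, and an interval for the rate needs the actual number of eligible patients as its denominator.

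**5. Adherence: why the unit matters.** Illustration with 21 people and 7 sessions, 21 × 7 = 147 sessions. If all 21 complete 5 sessions, the pooled figure is 105/147 = 71.4%. If 15 complete all 7 and 6 complete none, it is also 15 × 7 / 147 = 105/147 = 71.4%. If those 6 are left out of the denominator, it becomes 105/105 = 100%. The definition in the Feasibility section fits all three calculations.

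**The case against.** The case against has real force.

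- **Condensed article.** The list of descriptive statistics is introduced as examples, so intervals are not excluded, and a fuller protocol or analysis plan may specify them. This stands as a limit: the point is an improvement to the stated method, not proof that intervals will be absent.
- **No decision rule.** The targets are worded as aims, and no stop/go or progression criterion depends on them. This stands and lowers the stakes. It does not remove the use that readers will make of the figures.
- **Status of feasibility.** It shares the primary question with acceptability, and Table 1 lists the feasibility logbook in the qualitative column. That is so, but the logbook data are percentages and two of them have numerical targets.

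Stronger readings are tempting, and the documents do not support them:

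- A reader might infer that meeting or missing the target is mostly luck throughout. Step 3 shows that this fits only true rates near the target.
- A reader might count every miss between 70% and 80% as an error. At a true rate of 70%, which is below the 75% target, a miss is the correct result.
- A reader might treat 21/30 as the recruitment rate and put an interval on it. That describes the defined rate only if exactly 30 eligible patients are approached, which is stated nowhere.
- A reader might infer that adherence will be pooled over sessions and then look falsely precise. Pooling is not stated, no within-person correlation is given, and adherence has no target to meet or miss. What remains is that its unit and denominator are open.

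**Conclusion.** The point holds in limited form, as a cheap improvement to the analysis of a primary feasibility measure. Near its own 75% target, a retention percentage from 21 to 30 people cannot separate adequate from inadequate retention: the exact 95% interval at the target spans about 32 to 39 points, and the chance of reaching 16 of 21 runs from 36% to 77% as true retention goes from 70% to 80%. Clearly low or clearly high retention would still show. The calculation assumes independent participants, a 95% level and a denominator of 21 or 30; with 20 enrolled by April 2025 (Results), the lower figure is the more likely one. For recruitment, the defined rate and the target count need to be kept apart. For adherence, the unit and denominator need to be fixed.

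**What to change.** Add to the Analysis section:

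1. Report retention with numerator, denominator and an exact or Wilson 95% confidence interval. Read the 75% target against that interval: clearly met, clearly missed, or compatible with both.
2. Report recruitment as agreeing over eligible patients, with the actual denominator and the same type of interval. Report separately how many of the desired 30 were enrolled, against the target of 21.
3. Summarise adherence per participant over everyone enrolled, drop-outs included: sessions completed out of 7, with median, range and the number reaching each session. Report activities separately from sessions.

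This changes analysis wording only and needs no new participants or measurements, provided that the logbook holds the number of eligible patients and each person's completed sessions. The price is a less definite statement on whether the targets are met: at 16/21 the conclusion would be that the data are compatible with retention both below and above 75%.
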